### Changes in physical activity

Changes in accelerometer-measured moderate-vigorous physical activity (minutes/week) and in AWAS planned moderate-vigorous physical activity and brisk walking (minutes/week) will be analysed using repeated-measures models. Preliminary descriptive analyses will consider the longitudinal trajectories of participants to determine the homogeneity of trajectories and identify outliers. We will fit the repeated measures models using a generalised estimating equations framework. Estimates of the main effects of time by intervention will be used to assess the impact of intervention on each outcome. Possible attrition bias will be assessed using a longitudinal model with a binary dependent variable of dropout at each assessment time. This model will include time-independent covariates such as age, and time-dependent covariates such as previous physical activity.

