## Methods

### Study design

MobileMums is being evaluated in a 9-month, two-arm community-based randomised controlled trial. Participants are recruited on a rolling basis and randomly allocated to one of two study groups: the MobileMums intervention group or usual care control group. Data are collected before the program begins (T1), immediately post-intervention (T2, 3 months post baseline), and after a 6-month no contact maintenance period (T3, 9 months post baseline)*.* The final T3 data were collected in December 2012, and the trial is ongoing with further qualitative assessment of program impact. The trial was designed and will be reported in accordance with the CONSORT guidelines for reporting randomised controlled trials [28], and is registered with the Australian New Zealand Clinical Trials Registry (ACTRN12611000481976). Ethical clearance for this research was obtained through the Queensland University of Technology Human Research Ethics Committee.

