### Primary outcome

The primary outcome is change in moderate-vigorous physical activity (RQ 1). This outcome is being assessed objectively by accelerometer and subjectively through a telephone-administered questionnaire. The accelerometer provides an objective estimate of total accumulated moderate-vigorous physical activity, whereas the self-report questionnaire assesses specific types of moderate-vigorous activity (e.g., brisk walking for exercise). It was important for us to include this self-reported measure of women’s activity, since most women in the pilot study chose to set a SMART exercise goal specific to brisk walking [27], and the accelerometers cannot isolate walking from other moderate intensity activity. Also, MobileMums targets increases in structured, leisure-time physical activity, and the self-report measure allows us to examine activity reported within this domain, while the accelerometer does not differentiate between activity domains.

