### Questionnaire

The Australian Women’s Activity Survey (AWAS) is administered during the telephone interview and was developed to specifically assess physical activity among women with young children [32]. The AWAS assesses women’s typical weekly activity in the past month across five domains (planned, transport, childcare, domestic and work-related) and three intensity levels (light, moderate and vigorous). The interview-administered AWAS has good test-retest reliability (ICC=0.80 (0.65–0.89)) and acceptable criterion validity (compared to accelerometer data; r^s^=0.28, p=0.01) for measuring planned weekly physical activity among women with young children [32]. The key variables that will be extracted from the AWAS are: minutes per week of Planned Moderate-Vigorous Physical Activity; and, minutes per week of Brisk Walking for Exercise. The research staff administering the AWAS received training and conducted role plays before collecting participant data. Throughout the trial, research staff record (with participant consent) two telephone interviews on three separate occasions. A study investigator (BF) listens to these recordings and provides feedback on the AWAS administration in an attempt to increase script fidelity and reduce inter-interviewer variability.

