### Data analyses

Data analyses will follow intention-to-treat principles [28], so all participants will be analysed according to their randomised group regardless of whether they complied with the program or not. Missing physical activity data will be imputed using a model that accounts for the often skewed distribution of physical activity. Missing data will be imputed using a regression model based on time and a subject’s previous responses using a random intercept. To account for the uncertainty in imputing missing data the analyses will use multiple imputation using the WinBUGS software. Statistical significance will be set to 5% and 95% confidence intervals will be given for all results.

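### RQ1 rests on three unranked measures at two follow-ups, all at 5%, so if any one significant result counts as success the false-positive risk is about 11–14% or 18–26%, depending on how time is tested

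*Protocol article*

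**What the plan says.** All references are to the Protocol article.

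- **Background** states RQ1 as a single question: whether the improved program raises moderate-vigorous physical activity (MVPA).
- **Primary outcome** names one outcome, change in MVPA, and then gives it two instruments: "This outcome is being assessed objectively by accelerometer and subjectively through a telephone-administered questionnaire". It explains why both are kept but does not say which one leads.
- **Questionnaire** takes two variables from the AWAS: "minutes per week of Planned Moderate-Vigorous Physical Activity; and, minutes per week of Brisk Walking for Exercise".
- **Changes in physical activity** treats all three measures alike: "Changes in accelerometer-measured moderate-vigorous physical activity (minutes/week) and in AWAS planned moderate-vigorous physical activity and brisk walking (minutes/week) will be analysed using repeated-measures models". The effect is then described as follows: "Estimates of the main effects of time by intervention will be used to assess the impact of intervention on each outcome".
- **Study design** sets follow-ups at 3 months (T2, end of intervention) and 9 months (T3, after six months without contact). Neither is called primary.
- **Data analyses** gives one threshold: "Statistical significance will be set to 5% and 95% confidence intervals will be given for all results".
- **Sample size** rests on a 40 minutes/week increase on the AWAS, a spread of 102 minutes/week, two-sided 5% and 80% power, giving 102 per group. It does not say which AWAS variable or which follow-up is meant.

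**The concern.** One efficacy question can be answered by up to six results (three measures, two times), and nothing fixes in advance which of them answers it. The sample size treats the trial as one comparison at 5%, but the analysis sections do not reduce it to one.

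The article also leans both ways on which measure should lead. The sample size is built on the AWAS, and the Primary outcome section says the AWAS can isolate the structured leisure-time activity that the program targets. Against that, the Background lists the lack of objective measurement as a limitation of the pilot, and the Discussion bases the trial's claim to more valid evidence on objective measures. If the two instruments disagree, both readings could be defended after the fact. The Questionnaire section reports a correlation of only 0.28 between AWAS planned activity and accelerometer data, so disagreement is a realistic prospect.

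The results are meant to decide whether further investment in translating the program is warranted, so a choice of measure or time point made after seeing the data would feed straight into that decision.

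**Working it through.** **1. The plan's own figure.** Inputs from Sample size: difference 40, spread 102 (called a variance in the text, but it reproduces the figure only as a standard deviation), two-sided 5%, 80% power.

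n per group = 2 × [102 × (1.960 + 0.842) / 40]² = 102.07.

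This agrees with the stated 102. The trial is therefore sized for exactly one comparison at two-sided 5%.

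**2. How many tests bear on RQ1.** The text on time by intervention allows two readings:
- (a) one joint test across both follow-ups for each measure: 3 tests;
- (b) a separate contrast at T2 and at T3 for each measure: 3 × 2 = 6 tests.

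**3. Upper values, assuming independent tests.** The error is 1 − 0.95^k.
- k = 3: 1 − 0.95³ = 14.3%.
- k = 6: 1 − 0.95⁶ = 26.5%.

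**4. With correlated tests.** Correlated null z-statistics for three measures at two times were simulated, with 1,000,000 draws per setting. The assumed ranges were:
- accelerometer with AWAS: 0 to 0.5, including 0.28;
- planned MVPA with brisk walking: 0.3 to 0.85;
- T2 with T3: 0.3 to 0.7.

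| Reading | Independent | Full assumed range | Accelerometer–AWAS at 0.28 |
|---|---|---|---|
| (a) one joint test per measure | 14.3% | 11.3–14.0% | 12.0–13.8% |
| (b) each follow-up separately | 26.5% | 18.1–25.5% | 19.2–25.0% |

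All entries assume no true effect on any measure, and that any one significant result is read as success.

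**5. Cost of the repairs**, using 40/102 for every test and 102 evaluable women per group. The expected z-value is (40/102) × √(102/2) = 2.80.
- One lead test at 5%: Φ(2.80 − 1.96) = 80%.
- Two co-primary tests under Holm, first step at 2.5%: Φ(2.80 − 2.24) = 71%.
- Bonferroni over three (1.67%): 66%, or 137 per group to restore 80%.
- Bonferroni over six (0.83%): 56%, or 158 per group to restore 80%.

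**The case against.** Four points can fairly be made for the plan.

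*The test structure is not stated.* A reader might infer that six separate 5% tests are planned and that an error of 20% or more is built in. The article does not say so. Its wording fits one joint test per measure equally well, and that roughly halves the figure. This objection stands, which is why two ranges are given.

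*No rule says that one significant result is enough.* The measures have different roles: total activity for the accelerometer, structured activity and walking for the AWAS. T2 and T3 address end-of-program effect and maintenance. A confidence interval is promised for every result. This stands in part: the any-one-counts reading is neither stated nor ruled out. But RQ1 is not divided along those lines, and the three measures sit together under one primary outcome.

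*The 0.28 is stretched if used as an input.* It is a rank correlation from a validity study of AWAS planned activity against accelerometer data. It is not a correlation between treatment-effect estimates, and it is not given for brisk walking. This stands, so 0.28 is only one value within a wider assumed range.

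*An analysis plan that is not shown may rank the tests.* That is possible, and a missing multiplicity procedure would not be a finding in itself. But the article has a section defining the primary outcome, and that section leaves two instruments level. It also sets 5% for all results. It labels the mediator and moderator analyses exploratory, so it does rank analyses elsewhere, but not here.

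**Conclusion.** The point holds. One named primary outcome is carried by three unranked measures at two unranked times, at a flat 5%, in a trial sized for one 5% comparison. Followed as written, the plan does not hold the RQ1 claim at 5% and has no rule for discordant results.

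The size is conditional: about 11–14% with one time-by-intervention test per measure, and about 18–26% if each follow-up is tested separately. Both ranges require that any one significant result counts as success, and both rest largely on assumed correlations. Even the lower range is more than twice the nominal 5%.

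Two stronger statements are not supported. The higher range cannot be given as the plan's error rate, because six separate tests are an inference. Nor can AWAS planned MVPA at T2 be called the measure on which the sample size was built, because the Sample size section names neither the AWAS variable nor the time point.

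**What to change.** Before any between-group comparison is run, the investigators should record one of the following, with a date. The date matters because Study design says T3 collection ended in December 2012.

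- **Fixed order.** Name one lead measure and one lead time point for RQ1. Test the other measure and the other time point in a stated order, each at 5% and only if the preceding test is significant.
- **Co-primary.** Keep accelerometer MVPA and AWAS planned MVPA as co-primary at one named time point, with Holm.

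In either case, report brisk walking as secondary with a confidence interval, and say whether time by intervention is a joint test or a contrast at a named follow-up.

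The choice of lead measure belongs to the investigators, since the article gives grounds for either. If the AWAS leads, state which AWAS variable and time point the sample size refers to. If the accelerometer leads, say so, and note that Sample size expected the AWAS to require the larger sample.

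The change is to analysis wording only. A fixed order costs the lead test no power (80% at 102 per group), but later tests cannot be claimed as confirmatory once an earlier one fails. Holm over two tests avoids that dependence, at the price of power for a single 40-minute effect falling from 80% to about 71% at 102 per group.

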### Randomisation

In order to achieve similar groups, subjects were randomised in strata according to their baseline physical activity. Baseline physical activity was determined using T1 data from a single item physical activity assessment. The question asks participants to indicate (on a scale from 0–7 days) how many days per week (in the past 3-months) they “exercised for at least 30-minutes”. This single-item question has acceptable criterion validity against Actigraph GT1M accelerometer data (r^s^=0.38, p<0.001) for assessing days per week of at least 30-minutes of moderate-vigorous physical activity in women with young children. We used the data from this brief assessment for stratifying randomisation and not the more detailed T1 physical activity data as the brief assessment is more likely to be used by health agencies in the future to identify potential participants. Each participant was classified as either: not at all active (exercised 0 days per week); somewhat active (exercised between 1 and 4 days per week) or sufficiently active (exercised 5 days or more per week). Randomisation was managed by the project coordinator using lists created by the R software package using random permuted blocks of size ten.

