### Sample size

Our sample size was based on the clinically meaningful increase in physical activity (assessed by the AWAS) observed in our pilot study (40 minutes/week) [27]. We chose to base the sample size on self-report physical activity data, not the objective accelerometer data, because our pilot data suggested the AWAS was likely to produce the higher sample size estimate due to larger variance. Using the variance observed in the self-report data of 102 minutes/week [27], and assuming 80% power and two-sided significance of 5% we needed 102 women per group. Estimating a 25% dropout, this figure was inflated to 128 per group, or 256 total.

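### The time-by-intervention GEE names no adjustment for baseline activity or randomisation stratum; read naturally it is an unbiased change-score contrast that gives up a fraction (1 − ρ)/2 of the variance

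*Protocol article*

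**What the plan says.** The Primary outcome section defines the outcome as change in moderate-vigorous activity, measured by accelerometer and by the AWAS questionnaire. The section Changes in physical activity puts these changes into repeated-measures models fitted by GEE and then states: "Estimates of the main effects of time by intervention will be used to assess the impact of intervention on each outcome". It lists covariates for a separate model of dropout (age and earlier activity, as examples) but none for the effect model.

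The Randomisation section says that "subjects were randomised in strata according to their baseline physical activity". The three levels (0, 1–4, and 5 or more days a week) come from a single T1 item.

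The text does not say whether T1 is a response, whether the arms have separate baseline means, which working correlation is used, or whether baseline activity or stratum is adjusted for.

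**The concern.** A change outcome whose effect is read from a time-by-intervention term most naturally means a model with T1, T2 and T3 as responses and a free group difference at T1. That model subtracts the whole observed baseline difference between arms. In a randomised trial that difference is chance, and subtracting all of it is too much when ρ is below 1. Adjusting for baseline subtracts the right share.

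Precision on the primary outcome is at stake, not validity. According to the Study design section, the last T3 data were collected in December 2012, so the sample size can no longer change. The analysis is still described in the future tense, so the model is one of the few things left to improve. The strata were formed from baseline activity, so the design already treats it as prognostic, and the stated effect model does not carry this through.

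**Working it through.** **Inputs from the article.** Difference δ = 40 min/week (Sample size). Spread of 102 min/week, introduced as "Using the variance observed in the self-report data of 102 minutes/week"; the unit and the result show that it is an SD. The article does not say whether it is the SD of a single measurement or of change. Two-sided 5%, 80% power. Correlation of the stratifying item with accelerometer data, 0.38 (Randomisation). AWAS test-retest ICC 0.80, interval 0.65–0.89 (Questionnaire).

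**Assumed.** ρ, and equal variance s² at each time.

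**Step 1: the plan's own figure.** n = 2 × [102 × (1.960 + 0.842)/40]² = 102.07 per group, which reproduces "assuming 80% power and two-sided significance of 5% we needed 102 women per group". The inflated figure of 128 is 102 × 1.25 = 127.5. With 25% dropout, 128 × 0.75 = 96 per group remain, and power at SD 102 is 77.5%. I use 96 below.

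**Step 2: variance per woman.**
- Change score: 2(1 − ρ)s².
- Baseline-adjusted: (1 − ρ²)s².
- Ratio: (1 + ρ)/2, so adjustment removes (1 − ρ)/2.

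If the SDs are unequal (s₁ at baseline, s₂ at follow-up), the excess variance of the change score is (s₁² + s₂² − 2ρs₁s₂) − s₂²(1 − ρ²) = (s₁ − ρs₂)², which is never negative.

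**Step 3: results.** Power is by normal approximation at 96 per group, without then with baseline adjustment.

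| ρ | Change, ×s² | Adjusted, ×s² | Variance removed | SE removed | Power if 102 is SD of change | Power if 102 is SD of one measurement |
|---|---|---|---|---|---|---|
| 0.40 | 1.20 | 0.84 | 30% | 16% | 77.5% → 90.1% | 69.9% → 84.2% |
| 0.50 | 1.00 | 0.75 | 25% | 13% | 77.5% → 88.0% | 77.5% → 88.0% |
| 0.60 | 0.80 | 0.64 | 20% | 11% | 77.5% → 85.9% | 85.9% → 92.5% |
| 0.65 | 0.70 | 0.578 | 17.5% | 9% | 77.5% → 84.9% | 90.1% → 94.7% |
| 0.80 | 0.40 | 0.36 | 10% | 5% | 77.5% → 81.7% | 99.0% → 99.5% |
| 0.89 | 0.22 | 0.208 | 5.5% | 3% | 77.5% → 79.8% | both near 100% |

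**Step 4: which GEE does this?** In a simulation with an exchangeable working correlation (300 runs, 96 per group), the GEE with T1 as a response and a free group effect equalled the change-score contrast. Without the group main effect, so with a common baseline mean, the variance ratios were 0.70, 0.81 and 0.89 at ρ = 0.4, 0.6 and 0.8, against 0.70, 0.80 and 0.90 in theory. This depends on the working correlation. Under independence, the common-baseline model returns the raw follow-up difference, with variance s² instead of (1 − ρ²)s².

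**Step 5: the strata.** Take the correlation between the item and the baseline outcome as 0.38, and between the item and follow-up as between 0.38ρ and 0.38 (assumed). The two-predictor R² then gives the extra variance removed once baseline is in the model. It is 0% at the lower end. At the upper end, with ρ = 0.4, residual variance falls from 0.840 to 0.779, a further 7%; with ρ = 0.8 the further gain is 2%.

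**The case against.** The strongest reply is that this is a condensed article. It does not say that baseline or stratum is left out, and a full analysis plan may contain both. The wording also fits a common-baseline GEE, which loses almost nothing. This stands in part: the text cannot be said to exclude adjustment, and having T1 as a response is not in itself a fault. But the article does commit to an estimator, and its natural reading is the less efficient one.

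Four stronger readings are tempting and are not supported.

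- **A fixed loss of 20–30%.** This needs ρ between 0.4 and 0.6, which the article does not give. Its only within-woman figure, the AWAS ICC of 0.80 (0.65–0.89), implies 5.5–17.5%. That figure is test-retest reliability, and the correlation over 3 or 9 months may be lower, but this is an assumption.
- **Bias.** Under the natural reading the contrast is unbiased.
- **Dilution to two-thirds.** If the effect were the intervention main effect averaged over T1–T3, a constant 40 min/week would become (0 + 40 + 40)/3 = 26.7. The phrase is loose, but the section heading and the definition of the outcome as change point to the interaction.
- **Standard errors inflated by between-stratum variation.** In a change-score contrast, stable level differences between strata cancel; only stratum differences in change remain.

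The power gain is also conditional. If 102 is the SD of one measurement and ρ is 0.6 or more, the unadjusted analysis already exceeds 80%.

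**Conclusion.** The point holds as one of efficiency and wording. On the natural reading the planned effect is a change-score contrast with no stated adjustment for baseline or stratum, and adjustment would remove (1 − ρ)/2 of its variance. Over the values considered this runs from 30% (ρ = 0.4) to 5.5% (ρ = 0.89). The range rests on an assumed ρ and on equal variances over time; the direction does not depend on equal variances. If 102 is the SD of change, adjustment brings power at 96 per group from 77.5% to 80% or very close to it (79.8–84.9%) across the whole ICC interval. The stratum is a minor addition, of about 0–7%. Separately, the description of an interaction as a main effect should be corrected whichever model is intended.

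**What to change.** Before the arms are compared, specify one of two models for each activity outcome.

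1. A GEE on T2 and T3 with intervention, time, time-by-intervention, the baseline value of the same outcome, and the randomisation stratum (0, 1–4, 5 or more days).
2. Equivalently, a GEE on T1, T2 and T3 with baseline means constrained equal across arms, plus stratum. Here the working correlation must not be independence, or the gain is lost (Step 4).

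Replace the sentence on main effects with a statement that the effects are the adjusted between-group differences at T2 and at T3, each with its 95% confidence interval. If a fuller plan already specifies such a model, bring the article's wording into line with it.

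All variables are collected at T1. The cost is model specification only.

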### Cost-effectiveness analysis

Costs and QALYs will be modelled using a decision analytic Markov model [37], with due consideration of parameter uncertainty as described by probabilistic sensitivity analysis. One thousand random samples will be drawn from probability distributions and cost-effectiveness acceptability curves plotted for the two study groups to reveal the probability the program is cost-effective. This method has been used in previous cost-effectiveness studies [37,48,49].

